### Laboratory parameters

Laboratory tests are detailed in **Annex 6** and should be conducted according to the schedule of activities for each participant (**Table 1**). Any clinically significant findings from laboratory tests that result in a diagnosis and that occur after the patient receives the first dose of the investigational product should be reported by the PI/sponsor as an AE via eCRF. The samples processed and reported will be conducted as described for the secondary (and exploratory) outcomes. **See Subsection 9.4.1** for the definitions of the adverse events and when abnormal laboratory parameters will be considered adverse events.

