### Vital signs

Vital signs: heartbeat by pulse and blood pressure will be assessed as described for the secondary (and exploratory outcomes). In addition, the temperature will be measured at visits 1 and 2 to rule out infection.

For each participant, a 12-lead ECG will be collected. The electrocardiograms will be recorded after the participant has been supine for five minutes in a quiet room. Electrocardiograms will initially be interpreted by a qualified physician, the investigator, or a qualified designee at the site as soon after ECG collection as possible. Ideally, when the participant is still present for immediate action, should any clinically relevant findings be identified. Any clinically significant findings from ECGs that result in a diagnosis after the participant receives the first dose of the investigational will be reported as an AE via the eCRF. Copies of ECGs collected on thermal paper should source data and be properly stored.

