### 9.3.7 Phone Visit 4 – Follow-up

Intervention arm:

This visit will be conducted about two weeks after the end of the treatment period for follow-up and safety outcomes (AE/SAE assessment), only for the participant in the intervention arm.

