#### Reportable AEs for Hypoglycemia and Hyperglycemia/Diabetic Ketoacidosis.

**Hypoglycemia:** Hypoglycemia is common in people with T1D. Clinically significant hypoglycemia (Level 2), defined as a blood glucose concentration of <3.0 mmol/L (<54 mg/dL) for at least 15 consecutive minutes in the CGM, typically leading to neuroglycopenic symptoms, will be reported as an AE if other causes, such as meal omission, unexpected increases in physical activity, or exercise, miscalculations of boluses by the participant or any other contributing factors, have been excluded. A diary for hypoglycemia events will be provided to participants for recording BG levels measured before treatment administration if taken, associated symptoms, treatment administered, and information about contributing factors, if applicable, as described previously.

Only severe hypoglycemia (or hypoglycemia level 3), defined as "a hypoglycemia event requiring medical assistance of another person due to altered consciousness and requiring another person to actively administer carbohydrate, glucagon, or other resuscitative actions" is reportable as an SAE. This means that the participant was impaired cognitively to the point that he/she was unable to treat himself/herself, was unable to verbalize his/ her needs, was incoherent, disoriented, and/or combative, or experienced seizure or coma. These episodes may be associated with sufficient neuroglycopenia to induce seizure or coma. If plasma glucose measurements are unavailable during such an event, neurological recovery attributable to restoring plasma glucose to normal is considered sufficient evidence that a low plasma glucose concentration induced the event.

**Hyperglycemic events/Diabetic Ketoacidosis (DKA):** Hyperglycemic event is only reportable as an adverse event when one of the following four criteria is met:

- 1) The event involved DKA, as defined by the Diabetes Control and Complication Trial (DCCT) and described here:

Hyperglycemic events are classified as DKA if the following are present (meeting all 4 criteria):

- a) Symptoms such as polyuria, polydipsia, nausea, or vomiting
  - b) Serum ketones >1.5 mmol/L or large/moderate urine ketones
  - c) Either arterial pH <7.30 or venous pH <7.24 or serum bicarbonate <15
  - d) Treatment provided in a healthcare facility.
- 2) Evaluation of treatment was obtained at a healthcare provider facility for an acute event involving hyperglycemia or ketosis.

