### 11.2 Determination of Sample Size

Assuming a 1:1 randomization ratio, we calculated that a sample size of 42 participants (21 in each arm) would provide 80% power with a type I error rate (two-sided) of 5% to reject the null hypothesis with the following assumption: a standard deviation (SD) at baseline for TIR of 15%, a pre-post difference of TIR in the control group of 0.2%, a pre-post difference of TIR in the treatment group of 10.5%, a correlation of 0.7, and an attrition rate of 20%. The assumptions were taken from retrospective studies in T1D using tirzepatide (34,35).

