#### **11.4.5 Safety analysis**

The entire ITT population will be included for safety analysis (such as AE/SAE). A table will be populated with the frequency of system-wide adverse events between two groups. Differences in safety outcomes will be examined between ITT groups using Chi-Square tests for categorical outcomes (any AE/SAE, clinically significance hypoglycemia, severe hypoglycemia, DKA) and non-parametric tests for continuous variables with non-normal distribution such as time spent in hypoglycemia on CGM.

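### Laboratory and ECG adverse events are tied to a first drug dose that controls never receive, and adverse event follow-up is two weeks longer on tirzepatide, yet 11.4.5 compares the arms without a common window

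*Protocol*

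**What the plan says.** **Specific triggers.** In 9.2.4 (Laboratory parameters), the rule for clinically significant findings that lead to a diagnosis is that those "that occur after the patient receives the first dose of the investigational product should be reported by the PI/sponsor as an AE via eCRF". For ECGs, the text under Vital signs in 9.2.4 applies to a diagnosis "after the participant receives the first dose of the investigational will be reported as an AE via the eCRF". The definition of an adverse event in 10.1.1 is likewise worded for someone who has been given a pharmaceutical product.

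**General rules.** The Adverse events paragraph of 9.2.4 and the opening of 10.1.2 require all AEs and SAEs to be documented from consent to the last protocol-specific procedure, including safety follow-up. Neither restricts this to one arm.

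**Follow-up.** Table 1 places Visit 4 at week 16 and the safety call (P3) at week 18. Footnote a to Table 1 limits the call to the intervention arm, and 9.3.7 confirms that it is "only for the participant in the intervention arm".

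**Comparison.** Section 11.4.5 states: "Differences in safety outcomes will be examined between ITT groups using Chi-Square tests for categorical outcomes". The outcomes it lists are any AE/SAE, clinically significant hypoglycaemia, severe hypoglycaemia and DKA. It sets no observation window.

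**The concern.** Safety is part of the overall objective (4.1) and has its own objective (4.4), and 11.4.5 tests it between arms. Such a comparison is fair only if an event of the same kind, at the same time, would be recorded in either arm.

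The trial is open-label, so site staff know who has had a dose. Staff who follow the specific laboratory and ECG sentences would record those diagnoses on tirzepatide and not in controls. Staff who follow the general rule would record them in both arms. Arm A also has two further weeks in which an event can be counted. Both effects run in the same direction, against tirzepatide.

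**Working it through.** The protocol gives no figure for the safety comparison, so there is none to reproduce. The only design input is the arm size of 21, which was set for time in range: SD 15 × √(1 − 0.7²) = 10.71 and difference 10.5 − 0.2 = 10.3 give 17 per arm, and 17 × 1.2 = 20.4, rounded up to 21.

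**1. Do the ascertainment rules agree?**
- Visits 3 and 4 (9.3.4, 9.3.6) list the same laboratory tests, ECG and AE/SAE assessment for both arms, so the findings will exist in both.
- The general rules make such a diagnosis an AE in either arm. The specific sentences state a trigger only for participants who have had a dose.
- For when an abnormal laboratory value counts as an AE, 9.2.4 refers to Subsection 9.4.1. Chapter 9 ends at 9.3.8. The definition itself is in 10.1.1 and is also tied to having been given a product. Nothing resolves the conflict.

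**2. Effect of the unequal window.** On Table 1's timeline, counted from randomisation, the ratio is 18/16 = 1.125, or 12.5% more time. Counted from consent at about week −2 it is 20/18 = 1.111. With a constant hazard (assumed), a risk p over 16 weeks becomes 1 − (1 − p)^1.125 over 18 weeks. The last column is the exact probability, by binomial enumeration at 21 v 21, that an uncorrected chi-square test gives p < 0.05 when the hazards are equal.

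| Risk to week 16 | Risk to week 18 | Excess (points) | Chi-square rejects |
|---|---|---|---|
| 11.8% | 13.2% | 1.4 | 5.0% |
| 30% | 33.1% | 3.1 | 6.1% |
| 50% | 54.1% | 4.1 | 5.4% |
| 70% | 74.2% | 4.2 | 6.6% |

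The 11.8% is the severe hypoglycaemia incidence quoted in 9.2.5. The other risks are assumptions to show the range.

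**3. Effect if the dose-based sentences are followed literally.** Let both arms have the same true risk p of a laboratory or ECG diagnosis, recorded in arm A only. The recorded difference is p − 0 = p. With 0 of 21 in controls, chi-square is significant from 4 events upwards (4 v 0: p = 0.036), so the false-positive rate is P(X ≥ 4) for X ~ Binomial(21, p): 1.9% at p = 5%, 15% at 10%, 39% at 15% and 63% at 20%. The protocol gives no value for p.

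**4. Both together, for any AE.** Assume 30% have some other AE by week 16 and 10% have a laboratory or ECG AE, independently.
- Literal reading only: 1 − 0.7 × 0.9 = 37% recorded in arm A against 30% in arm B; false-positive rate 8.3%.
- With the extra two weeks: 1 − 0.63^1.125 = 40.5% against 30%; false-positive rate 11.5%.
- With equal 30% risks and equal recording, the same test rejects in 5.6% of trials.
- Over other-AE rates of 30% and 50% and laboratory/ECG rates of 5% to 20%, the combined false-positive rate runs from 6.7% to 22.2%.

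**The case against.** The strongest reply is that the general rules already cover everyone. The specific sentences say what should be reported and do not say that other findings are excluded, and the list of events that need not be reported (10.1.2.1) does not mention control-arm laboratory or ECG diagnoses. That stands. A reader might infer that laboratory and ECG events are zero by rule in the 21 controls. The documents support only a contradiction, which biases the comparison if sites follow the narrower sentence.

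It can also be said that the week-18 contact is a single safety call, that its effect is small, and that an SAP may fix the analysis window. The effect is small on its own. But the protocol itself sets both the one-arm call and the between-arm test, so the window belongs beside them.

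Two further inferences are tempting and do not hold.

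- **Hypoglycaemia.** Section 10.1.2 says that a Level 2 event "will be reported as an AE if other causes, such as meal omission, unexpected increases in physical activity, or exercise" and similar factors have been excluded. A reader might conclude that the between-arm hypoglycaemia outcome is filtered by an unblinded judgement. That rule governs AE reporting and names no arm. The safety outcome in Chapter 5 refers to Annex 10, which uses below 3.0 mmol/L for at least 15 consecutive minutes with no cause filter, and 11.4.5 lists this outcome separately from any AE/SAE. What remains is that 11.4.5 does not say which definition it uses.
- **Chi-square on sparse counts.** A 4 v 0 split gives p = 0.036 by chi-square and 0.107 by Fisher's exact test, so a reader might infer that chi-square declares differences too easily. With equal risks and equal recording at 21 v 21, its exact false-positive rate is 1.2% at the 4.8% DKA incidence quoted in 9.2.5, 4.6% at 11.8%, and at most 5.6% over risks of 1% to 50%. The choice of test does not bias the comparison.

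**Conclusion.** The point holds as an internal contradiction plus an unequal observation window. The laboratory and ECG sentences in 9.2.4 cannot be applied to controls as written and conflict with the general collection rules. Follow-up after randomisation is about two weeks longer in arm A, and 11.4.5 does not allow for this. Both features can only raise recorded events on tirzepatide relative to control.

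The window alone adds about 1 to 4 points for risks of 11.8% to 70%, and less for rarer events, if the hazard stays constant after the last dose. The laboratory and ECG effect depends on how sites read the text. It is nil if they follow the general rule and equals the true risk of such a diagnosis if they follow the specific one. The event rates in steps 3 and 4 are assumptions, not protocol figures. The documents do not establish that the safety comparison is already biased by rule, and the primary efficacy analysis is not affected.

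**What to change.** 1. In 9.2.4, Laboratory parameters and the ECG text under Vital signs: replace the first dose of the investigational product by randomisation, for both arms. Reconcile both sentences, and the adverse event definition in 10.1.1, with the general collection rules in 9.2.4 and 10.1.2. Correct the reference to Subsection 9.4.1.
2. In 11.4.5: compare adverse events from randomisation to Visit 4 (week 16) in both arms, and list events after Visit 4 separately. The arm A safety call can stay as it is.
3. Minor clarification in 11.4.5: state that the between-arm outcome for clinically significant hypoglycaemia uses the Annex 10 definition, without the cause exclusion in 10.1.2.
4. Optional: exact tests or exact confidence intervals for sparse outcomes.

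The cost is an amendment of wording and a note to site staff; no visits, tests or data are added. If participants have already been followed, control-arm laboratory and ECG results should be checked once for diagnoses that were not entered as adverse events.

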### Vital signs

Vital signs: heartbeat by pulse and blood pressure will be assessed as described for the secondary (and exploratory outcomes). In addition, the temperature will be measured at visits 1 and 2 to rule out infection.

For each participant, a 12-lead ECG will be collected. The electrocardiograms will be recorded after the participant has been supine for five minutes in a quiet room. Electrocardiograms will initially be interpreted by a qualified physician, the investigator, or a qualified designee at the site as soon after ECG collection as possible. Ideally, when the participant is still present for immediate action, should any clinically relevant findings be identified. Any clinically significant findings from ECGs that result in a diagnosis after the participant receives the first dose of the investigational will be reported as an AE via the eCRF. Copies of ECGs collected on thermal paper should source data and be properly stored.

## 9.2.5 Assessments in participants who prematurely stop the study.

### Individual participant-stopping criteria.

Study drug administration may be stopped for any of the following reasons:

- Three or more episodes (separated by at least 120 minutes) of clinically significant hypoglycemia (Level 2) within one day (defined as 00:00 – 23:59) of the study, after excluding other causes such as the omission of meals, unexpected increases in physical activity, or exercise (or any other contributing factor more likely than the IMP) (**See Annex 10**).
- One or more episodes of severe hypoglycemia (Level 3) (**See Annex 10**).
- One or more DKA events unrelated to the participant's AID system malfunction.
- Adjudicated hepatic or pancreatic AEs.
- Incidence of allergic and hypersensitivity reactions.
- If a participant misses three or more consecutive doses of tirzepatide due to intolerable GI symptoms (e.g., nausea, vomiting, or diarrhea) that could be reasonably attributed to the study drug, despite the mitigation plan (**See Annex 8**).
- If a participant is diagnosed with an active or untreated malignancy (other than basal or squamous cell skin cancer, in situ carcinomas of the cervix, in situ, or grade group 1 [that is, Gleason 6 or lower] prostate cancer) after randomization.
- Dehydration or renal acute events.
- Post randomization calcitonin value  $\geq 35$  ng/L and increased at least 50% over baseline.
- Supraventricular arrhythmias and cardiac conduction disorders.
- If a female participant becomes pregnant.
- Investigator decides that, in the interest of the patient, it is not medically acceptable to continue participation in the study.
- Participants with a normal BMI at baseline will be closely monitored during clinical visits. The medication will be reduced to 2.5 mg or discontinued if there is a weight gain that exceeds 5% of total body weight or if weight reduction is too rapid (defined as greater than 1% of total body weight per week) following clinical evaluation

**Table 1** describes the time points of assessment. For the definition of these AEs/SAEs and for follow-up and procedures for participants who prematurely stop the study, see **Subsection 10.1.2**.

Criteria for suspending or stopping the study.

More than three cases of severe hypoglycemia (level 3, see **Annex 10** for hypoglycemia classification) or more than one case of DKA which were not deemed due to the participant's AID system malfunction (For definitions, see **Subsection 10.1.2**). These criteria are based on exceeding the average incidence of severe hypoglycemia (11.8%) and DKA (4.8%) in patients with T1D, as reported in the Type 1 Diabetes Exchange Clinic Registry (88).

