**STUDY SCHEDULE****Table 1. Visit Schedule.**

|                                                                             | Screening | Randomization             | Treatment Period |    |    |    | Follow-up       |
|-----------------------------------------------------------------------------|-----------|---------------------------|------------------|----|----|----|-----------------|
| Visit (V) or Phone (P)                                                      | V1        | V2                        | P1               | V3 | P2 | V4 | P3 a |
| Weeks                                                                       | -2        | 0                         | 4                | 8  | 12 | 16 | 18              |
| Window (days)                                                               | -7        | 14 up to 21 days after V1 | ±3               | ±3 | ±3 | ±3 | ±7              |
| Subject-related information/ assessments                                    |           |                           |                  |    |    |    |                 |
| Informed consent                                                            | X         |                           |                  |    |    |    |                 |
| Inclusion/Exclusion                                                         | X         |                           |                  |    |    |    |                 |
| Randomization                                                               |           | X                         |                  |    |    |    |                 |
| Screen fail/withdrawal criteria                                             | X         | X                         | X                | X  | X  | X  |                 |
| Medical history/demography b                                     | X         |                           |                  |    |    |    |                 |
| Concomitant medications                                                     | X         |                           |                  |    |    |    |                 |
| Trial-related outcomes measures and downloads                               |           |                           |                  |    |    |    |                 |
| Weight, Height, Waist & Hip circumference                                   | X         |                           |                  | X  |    | X  |                 |

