## 2. ETHICAL AND REGULATORY ASPECTS

Type 1 diabetes (T1D) is a chronic disease with an increasing incidence and prevalence (1–3). Intensified insulin treatments have led to a significant reduction in the risk of development and progression of long-term microvascular complications in T1D (4,5). However, this intensification also leads to more hypoglycemia events and weight gain with an increase in cardiovascular risk factors (6,7).

This study will test the safety and efficacy of the dual glucose-dependent insulinotropic polypeptide/glucagon-like peptide-1 receptor agonist (GIP/GLP1-RA) (*Mounjaro*® [tirzepatide]) as an adjunct therapy in people with T1D with existing insulin therapy through automated insulin delivery (AID). The results of this study will make an important contribution to the care of patients with T1D by improving their self-management, reducing the T1D burden, and improving their quality of life. The trial may result in improved glucose control and weight loss for the participants, indicating the potential for this molecule to become part of standard care for T1D in the future. Participants will be provided with written informed consent and fully informed about the study, including the risk-benefit ratio (**See Section 3.1**). Their right to stop the procedures and withdraw the informed consent at any time during the study will be respected.

The sponsor will submit the protocol, the proposed patient information and consent form, and other study-specific documents to the “Ethikkommission Nordwest-und Zentralschweiz” (EKNZ) and Swissmedic before the study commencement. The clinical study will only begin once approval from all required authorities has been received. Any additional requirements imposed by the authorities will be implemented.

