Studies with adjunct therapies to intensified insulin treatments have been conducted to improve glucose control and reduce the risk of microvascular and macrovascular complications. Agents recently evaluated include GLP-1 RAs (30), dipeptidyl peptidase-4 (iDPP-4) (31), amylin analog (32), and sodium-glucose transporter-2 inhibitors (SGLT2i) (33). The GLP-1RAs and (GIP)/GLP1-RAs (or dual incretins) analogs have emerged as a promising therapy in T1D(30,34,35). These medications allow the reduction of plasma glucose with a very low risk of hypoglycemia (36). The principal mechanisms leading to reductions in plasma glucose concentrations are (i) glucose-dependent insulinotropic actions, (ii) suppression of glucagon hypersecretion except during episodes characterized by hypoglycemia, and (iii) a deceleration of gastric emptying, which is associated with marked effects on post-meal glycemic excursions (37). The GLP-1RA and (GIP)/GLP1-RAs, also induce early acute changes in appetite and satiety, a corresponding reduction in caloric intake, and weight loss (38,39).

The combination of GLP1Ras and GIP/GLP-1RAs with insulin therapy has been extensively evaluated in T2D (40,41). However, several randomized controlled clinical trials have also suggested a positive impact in T1D as adjunctive therapy to insulin (42–44). In a Metanalysis published in 2017, Wang et al. showed that GLP-1RAs in combination with insulin improve glycemic control and reduce insulin bolus dose and weight in T1D (45). In the same direction, The Lira Pump trial, a randomized, double-blinded, placebo-controlled trial, demonstrated that Liraglutide (a short-acting GLP1-RA) treatment reduced HbA1c, total daily insulin (TDI) dose, and body weight without increasing the risk of hypoglycemia in continuous subcutaneous insulin infusion (CSII)-treated patients with T1D and insufficient glycemic control (46)

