In the SURPASS trials, tirzepatide improved glycaemic control and body weight in adults with inadequately controlled T2D, including when used as a monotherapy, as an add-on to oral hypoglycemic agents, or as an add-on to titrated basal insulin. Reductions in HbA1c levels were seen as early as week four, nearing the maximum about week 24; fasting serum glucose (FSG) levels followed a similar temporal pattern. Treatment with tirzepatide also improved 7-point self-monitored blood glucose profiles relative to both placebo and active comparators and resulted in mean 2-h postprandial glucose levels that were generally within the normal range ( $\leq$  140 mg/dL) at the study end (78). Tirzepatide weight loss began by week four, did not plateau, was sustained for the duration of the trials, and was dose-dependent (78,79). These findings led to a significant increase in the number of patients achieving the target HbA1c proposed by diabetes clinical guidelines (80). Regarding safety and tolerability, tirzepatide was generally well tolerated as monotherapy or add-on therapy to oral hypoglycemic agents or basal insulin in adults with T2D in nine SURPASS trials, with a safety profile consistent with that of selective GLP-1Ras (81). In a head-to-head study that compares tirzepatide vs semaglutide (a potent long-acting GLP1RA); tirzepatide was non-inferior and superior to semaglutide for the mean change in the HbA1c level from baseline to 40 weeks with favourable tolerability and safety (82).

In TD1 the clinical evidence of tirzepatide is still insufficient. A retrospective proof of concept conducted by Kaan Akturk, et al. in (34) demonstrated that tirzepatide was associated with significant improvement in glycemic outcomes and reduction in weight without an increase in hypoglycemia or ketosis. Glycemic improvements were seen within the first three months. There was no clinically significant improvement

in HbA1C beyond three months, despite continuous weight reduction (dose-dependent). These data suggest that glycemic efficacy can be achieved in a short time frame with a 2.5 to 5 mg/week dose without further significant improvement with higher dosage and with adequate tolerability and safety. Consequently, randomized clinical trials are required to test the efficacy and safety of tirzepatide in T1D.

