## 7. STUDY POPULATION

### 7.1 Eligibility criteria

#### 7.1.1 Inclusion criteria

Participants fulfilling all the following inclusion criteria are eligible for the investigation:

- 1) Participants with diagnosed T1D for at least 12 months.
- 2) Aged between 18 to 65 years old (inclusive).
- 3) Currently on AID therapy for at least three months.
- 4) HbA1C  $\geq 6.5\%$  and  $\leq 10\%$ .
- 5) BMI  $\geq 23$  kg/m^2.
- 6) Willing to use once-weekly tirzepatide for at least 16 weeks (including up-titration)
- 7) Willing to wear a Dexcom G7 Sensor and share devices (AID) data uploads.
- 8) Willingness not to start any new non-insulin glucose-lowering agent during the trial (including metformin/biguanides, pramlintide, DPP-4 inhibitors, sodium-glucose cotransporter 2 inhibitors [SGLT2 inhibitors], and nutraceuticals).
- 9) A stable weight ( $\pm 5\%$ ) in the last 90 days or more before the screening and agree to not initiate a diet and/or exercise program during the study to reduce body weight other than the lifestyle and dietary measures for diabetes treatment.
- 10) Females with childbearing potential and males (if apply) must be willing to use reliable contraceptive methods (for the contraceptives study guidelines. **See Annex 7**)
- 11) An understanding and willingness to follow the protocol and signed informed consent.

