#### **7.4 Criteria for withdrawal/discontinuation of participants**

Participation in this research is voluntary. Participants may withdraw at will at any time. When withdrawing from the study, the participant should let the research team know that he/she wishes to withdraw. The participant is not required to provide a reason.

The investigator must stop the study intervention for the individual participant if any of the following criteria are met:

- Withdrawal of informed consent
- Confirmed pregnancy.
- Actively trying to become pregnant.
- Developing an allergic reaction to tirzepatide.
- If the inclusion and exclusion criteria are no longer met.
- Non-compliance with the study procedures, or
- At the investigators' judgment due to safety concerns (**See Subsection 9.4.1** for the definition of adverse events and other safety-related events).

After withdrawal, the participant will be given instructions on how to safely stop using the IMP and, eventually, on how to return to the previous treatment regimen correctly and safely. Instructions are also given on who to contact if any questions or concerns arise after study withdrawal. Any data collected until study withdrawal will remain coded for the analysis.

Withdrawn participants will not be replaced. However, at the investigator's discretion, re-screening is allowed within the recruitment period to complete 42 participants. Further information about the follow-up procedures is available in **Subsection 9.2.5**.

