### 9.3.6 Visit 4 – End of intervention

Both randomization arms:

During this visit, the study team will perform the following evaluations:

- Weight, height, waist & hip circumference, waist-to-hip ratio
- Vital signs (blood pressure and heart rate)
- ECG
- Body composition (BIA)
- MAFLD and Liver fibrosis assessment (FibroScan®)
- Urine pregnancy test
- Device downloads (CGM and pump data)
- AE/SAE assessment according to **Section. 10** (including assessment for clinically significant hypoglycemia, severe hypoglycemia, and DKA).
- The hypoglycemia diary will be collected and reviewed.
- Questionnaires (DTSQc), the participant will complete a paper questionnaire, and the study staff will enter the data in REDCap.
- Laboratory tests including total bilirubin, indirect and direct bilirubin, ALT, AST, pancreatic serum amylase, serum lipase, creatinine with eGFR (calculated by CKD-EPI), uACR, calcitonin, HbA1c, CT, LDL, HDL, and triglycerides.

At visit 4, all the study devices will be returned.

Intervention arm:

The participant's medication logbook will be reviewed and collected. As well as the IMP's used pens.

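### In Protocol 9.2.5 the 5% weight trigger for participants with normal baseline BMI is set on gain, not loss, so loss has no total limit

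*Protocol*

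**What the plan says.** The last bullet of the individual stopping criteria in Protocol 9.2.5 covers participants with a normal BMI at baseline. After clinical evaluation, their dose is to go down to 2.5 mg or be discontinued "if there is a weight gain that exceeds 5% of total body weight or if weight reduction is too rapid". Rapid reduction is defined as more than 1% of body weight per week. The 5% total limit therefore applies to gain, and loss has only a rate limit.

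Elsewhere the protocol describes the drug's effect on weight in one direction:

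- Section 2 tells the reader: "The trial may result in improved glucose control and weight loss for the participants".
- Section 3.1 attributes to the drug class changes in appetite and satiety, "a corresponding reduction in caloric intake, and weight loss".
- Section 3.4 reports from the type 2 diabetes trials: "Tirzepatide weight loss began by week four, did not plateau".

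Table 1 has a row "Weight, Height, Waist & Hip circumference", marked at V1 (screening), V3 (week 8) and V4 (week 16). V4 is headed "Visit 4 – End of intervention". No weight is scheduled at V2, when treatment starts.

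Section 7.4 also requires the investigator to stop the intervention under this condition: "If the inclusion and exclusion criteria are no longer met". The entry criteria in 7.1.1 include a BMI of at least 23 kg/m² and an HbA1c of at least 6.5%.

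**The concern.** The bullet singles out the participants with the least weight to lose, who are given a drug expected to reduce weight. A total limit on loss would be the natural safeguard for them. As worded, the total limit triggers on gain, and the action is to reduce or withdraw a weight-lowering drug. Where the protocol mentions weight gain (Sections 2 and 3.1), it does so in connection with intensified insulin treatment and type 1 diabetes generally. The tirzepatide side-effect text in 3.7 does not list it.

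This is the only weight-specific safety rule for these participants. If it is applied as written, a steady loss below the weekly rate can pass the one scheduled weight check that still matters for dosing. The participant then continues at 5 mg for eight more weeks with no further scheduled weight until treatment ends. The efficacy inference is not at stake.

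**Working it through.** The plan gives no figure to reproduce here. The check is how much loss the bullet permits at V3, and how far other provisions close the gap.

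**Inputs from the protocol.** Rate limit 1% per week and total limit 5%, for gain (9.2.5); V3 at week 8 ± 3 days, V2 14 to 21 days after V1, and weights at V1, V3 and V4 (Table 1); entry BMI at least 23 (7.1.1); stop when entry criteria are no longer met (7.4).

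**Assumptions.** The protocol gives no interval for the weekly rate. I average it from first dose to V3, using the V1 weight because none is scheduled at V2. The protocol does not define normal BMI; I take its upper end as just below 25.

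**Step 1: loss needed to meet the rate limit at V3.** Compounded, the threshold is 1 − 0.99^w for w weeks.

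| Interval | Calculation | Loss needed |
|---|---|---|
| 8 weeks | 1 − 0.99^8 | 7.7% |
| 53 days (7.57 weeks) | 1 − 0.99^7.57 | 7.3% |
| 59 days (8.43 weeks) | 1 − 0.99^8.43 | 8.1% |
| 8 weeks, simple sum | 8 × 1% | 8.0% |
| 4 weeks, if an unscheduled weight is taken | 1 − 0.99^4 | 3.9% |
| 10 weeks, counted from V1 | 1 − 0.99^10 | 9.6% |
| 11 weeks, counted from V1 | 1 − 0.99^11 | 10.5% |

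On the 8-week reading, a loss between 5% and 7.7% at V3 meets nothing in the bullet. A 5% loss over 8 weeks is 5/8 = 0.63% per week, well under the rate limit. A gain of 5.1% over the same time does meet the bullet.

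**Step 2: the gap if 7.4 is read literally.** The drug then stops once BMI falls below 23. The loss that reaches 23 from entry BMI b is 1 − 23/b.

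- Setting this equal to 5% gives b = 23/0.95 = 24.2. Entrants from 23.0 to 24.2 reach the stop at or before a 5% loss.
- b = 24.5: 1 − 23/24.5 = 6.1%.
- b = 24.9: 1 − 23/24.9 = 7.6%.

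The uncovered group is then entry BMI of about 24.2 to 24.9, who can lose more than 5%, up to 7.6%, with no rule met.

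**Step 3: the gap if 7.4 is not applied to on-treatment BMI.** Any normal-BMI entrant can lose 5% to about 7.7% by V3 with only investigator discretion as a guard. From BMI 23.0 that means a BMI of 23 × 0.95 = 21.9 down to 23 × 0.99^8 = 21.2.

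**Step 4: is 7.4 a weight rule?** The entry criteria are introduced as conditions of entry: "Participants fulfilling all the following inclusion criteria are eligible for the investigation". Applied on treatment, the clause would also stop a participant whose HbA1c fell below 6.5%, which is a treatment success. It is hard to read it as a designed weight limit.

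**The case against.** The strongest objection is that the intent is inferred. Weight gain is a recognised concern in type 1 diabetes and the protocol says so, and no passage supplies a 5% loss limit. On that view the sponsor should only be asked to confirm the direction. It stands to this extent: the protocol does not state that loss was meant. But no passage justifies stopping tirzepatide for gain, and the absence of a total loss limit is a fact whichever direction was meant.

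Second, the practical gap is narrow. The investigator may stop the drug in the patient's interest, 9.3.8 allows unscheduled visits, the bullet itself calls for clinical evaluation, and 7.4 may catch many of these participants. No passage forces continued dosing during a worrying loss, and the BMIs derived above are not shown to be harmful. This limits the severity. It does not supply the missing threshold.

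Third, the 7.7% depends on the assumed interval. That is correct: the table runs from 3.9% to 10.5%, and at 3.9% a 5% loss limit would add nothing. The spread arises because the bullet does not fix the interval.

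Fourth, 8.3 forbids dose modification after stabilization, a term it does not define, and Annex 8 counts weeks 0 to 8 as escalation. So it is not established that 8.3 blocks the 2.5 mg option at V3. That is fair; the two texts meet at the week-8 boundary, and a clarifying clause removes the doubt.

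Fifth, a loss trigger would move some participants in an arm of 21 to 2.5 mg. This could slightly dilute the 5 mg estimate and affect who counts as per protocol under 11.4.1. That cost is real and belongs with the fix.

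**Conclusion.** The concern holds. The total-weight trigger is written for gain, no reason is given, and loss has only a weekly rate limit with no stated interval. That loss was intended is a well-supported inference, not something the protocol states.

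With the rate averaged from first dose to V3, the bullet misses losses from 5% to about 7.7% (7.3% to 8.1% across the visit window). With 7.4 read literally and normal BMI ending just below 25, this shrinks to entrants with BMI of about 24.2 to 24.9 and losses of up to 7.6%. The error should be corrected because it concerns a safety decision rule and is simple to put right. Nothing in the sample size, type I error, ITT set or primary analysis method depends on it.

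**What to change.** - In the last bullet of 9.2.5, replace the 5% gain trigger with a loss of more than 5% from the V1 body weight.
- Keep the 1% per week limit, state the interval over which it is computed, and apply both limits at the existing weight visits.
- If a limit on gain is truly wanted, give the reason and add the loss trigger beside it.
- In 8.3, exempt this bullet from the ban on dose modification after stabilization, so that 2.5 mg is clearly available at V3.

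The cost is a wording change in one bullet and one clause in 8.3, with no new visits or measurements and no change to the sample size or the primary analysis. The downside is some additional dose reductions or stops among normal-BMI participants on tirzepatide. The documents give no basis for estimating how many. These could slightly dilute the 5 mg comparison and reduce the per-protocol set.
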